### Data collection

Professional caregivers are asked to fill out the interRAI Home Care instrument. Clients fill out the WHO-QOL-8 and the main informal caregivers complete the ZBI-12. These questionnaires are filled out at inclusion of the frail older person in the project (baseline), at exit from the project and 6 months after baseline. Additionally, if clients stay longer than 6 months in the project, caregivers have to do a follow-up every 6 months until the moment clients leave the project. Follow-up of clients happens from March 2011 until July 2013. A client follow-up period will vary between 6 to 36 months. Criteria to exit the cohort will be institutionalization longer than 3 months and death. Follow up will also end for clients who leave the projects.

Professional caregivers are instructed on how to fill out the questionnaires during a 2-day training and a follow up training of 1 day. They fill out the interRAI HC based on observation and on interview of the older person and of the main informal caregiver.

The interRAI-data will be linked with data from the national database IMA (Inter-mutuality Agency). This database contains data on national health service consumption reimbursed by NIHDI such as medication use, hospital days, medical, nursing and physical therapy use, etc. This data will be added to the analysis for the clients in the projects.

The “permanent sample” of people over 65 extracted from IMA database will also serve as a control group for our study population. By using this database we will be able to compare older persons who are benefiting from the innovative projects with older persons who are not benefiting from these projects (control group). In this control group we will have two major groups – clients who are still living at home and clients who are institutionalized. All clients who are in the projects and have not given their informed consent will be excluded from this database.

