 The cognitive performance scale (CPS2) is an internationally validated scale that describes a person’s cognitive status. The scores vary from 0 to 6 and the scale consists of 5 items from the interRAI HC instrument: skills for daily decision-making, making oneself understood, short-term memory recall, procedural memory and eating impairment. Higher scores indicate a greater degree of cognitive impairment. Several studies have shown a significant correlation between the CPS scale and the Mini-Mental State Examination (MMSE) [38-41].

 – Research question 4 - Which types of projects are associated with a decreased risk of institutionalization of frail older persons?

In order to answer the fourth research question, the definitive institutionalization (more than 90 consecutive days in residential care) will be used as event. The analysis consists of the calculation of incidence rates, cumulative incidence and hazard rates of definitive institutionalization through survival analyses for each type of project. Survival analysis measures the time to a certain event or change of state, in this case, institutionalization. The multivariate Cox model which will be calculated from this analysis will allow us to isolate the effects of the intervention from the effects of confounding variables. These variables are extraneous variables which correlate (positively or negatively) with both the dependent variable and the independent variable. In this analysis we will use the variables of Table 2 as confounding variables. The use of a Cox model may improve the estimate of the intervention effect by narrowing the confidence interval. Another important advantage of this analysis is that it takes into account the variability of covariates across time which makes it very appropriate for longitudinal studies [42-44].

 – Research question 5 - Is the interRAI Maple scale a good predictor of institutionalization in our study?

The fifth research question will be approached by using a multiple logistic regression model with the Methods for Assigning Priority Levels scale (Maple) as one of the independent variables. This interRAI scale is known to be a predictor for institutionalization and can be used as an indicator for allocation of home care resources and prioritization of clients needing community or residential care. MAPLe is an internationally validated predictor of nursing home placements, caregiver distress and ratings that the client would be better off elsewhere [45].

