## Discussion

This paper describes the study protocol of a longitudinal quasi-experimental research to evaluate the effect of innovative projects in delaying institutionalization of frail older persons.

A major strength of the study is the follow up period of 3 years, which allows researchers to obtain a large sample size and several measurement points for a number of clients. Most clients will have at least 3 measurements. Another major strength is the availability of the national database IMA to enable researchers to have a large control group and to have data on health services and medication consumption of the study population. In addition, the use of international validated instruments such as the ZB-12 item, the WHOQOL 8 and the interRAI HC will also make further cross-national comparisons possible.

Some limitations of the study are due to the lack of randomization in the allocation between projects and due to the fact that not all variables collected in the population of the projects will be found in the control group of older persons not benefiting from the projects.

The research will provide knowledge on the functional situation of frail older persons who are still living at home and will allow researchers to make comparisons with older persons who are already institutionalized. This is important information to identify determinants of risk for institutionalization. The identification of effective projects in delaying institutionalization will be useful to inform and empower home care providers, policy and related decision makers to manage and improve home care services.

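### The 90-day event leaves out clients who enter residential care and die there before day 90, which can distort the comparison of project types

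*Protocol article*

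**What the plan says.** The Analyses section (research question 4) of the protocol article sets the event: "the definitive institutionalization (more than 90 consecutive days in residential care) will be used as event". The Data collection section applies essentially the same threshold to leaving the cohort and puts death beside it as a separate exit: "Criteria to exit the cohort will be institutionalization longer than 3 months and death". It adds: "Follow up will also end for clients who leave the projects".

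The event then feeds the "calculation of incidence rates, cumulative incidence and hazard rates of definitive institutionalization through survival analyses for each type of project". A multivariate Cox model follows, for which the article says: "In this analysis we will use the variables of Table 2 as confounding variables". Table 2 lists civil status, age, gender, quality of life, financial difficulties, caregiver burden, and scales for function, communication, cognition and mood. It has no diagnosis, comorbidity or prognosis variable.

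The Discussion names the "lack of randomization in the allocation between projects" as a limitation.

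**The concern.** A duration threshold is there to separate a permanent move from a temporary stay. As written, it also requires the client to survive more than 90 days in residential care. Survival says nothing about whether the move was permanent. A client who gives up the home and dies in residential care on day 40 did not stay at home, yet leaves the cohort as a death.

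The study's main goal is to find which types of project do most to delay institutionalization. If the share of admissions that end in death before day 90 is the same in all types, each type loses the same fraction of its events and the ratios between types are unaffected. If the share differs, the loss differs between the groups being compared, and the types could be ranked partly on early mortality after admission.

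This is a matter of how the event is classified. A competing-risk analysis would still code the day-40 client as a death, and longer follow-up would not change that client's status.

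**Working it through.** **Figures in the plan.** The article gives no institutionalization rate and no mortality after admission, so there is no event figure to reproduce. Its sample size (75 per group for an effect size of 0.50, two-sided 0.05, 85% power) uses no event rate and does not change. A two-sample t-test calculation gives 73, close to the stated 75.

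**Reading the rules together.**

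| Client | Status under the stated rules |
|---|---|
| Admitted, still resident after day 90 | Event |
| Admitted, returns home before day 90 | No event (intended) |
| Admitted, dies in residential care on day 40 | Death, no event |
| Dies at home | Death, no event |

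The third and fourth clients are treated alike, although only the fourth stayed at home.

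**Size, unadjusted.** Let m1 and m2 be the shares of admissions ending in death before day 90 in two types, and R the true ratio of admission rates (type 2 to type 1). Counted events are then a fraction 1 − m of admissions, so approximately

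apparent ratio = R × (1 − m2)/(1 − m1).

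All values of m and R below are assumptions.

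| m1 | m2 | R | Apparent ratio |
|---|---|---|---|
| 10% | 10% | 1.00 | 0.90/0.90 = 1.00 |
| 10% | 15% | 1.00 | 0.85/0.90 = 0.94 |
| 5% | 15% | 1.00 | 0.85/0.95 = 0.89 |
| 10% | 25% | 1.00 | 0.75/0.90 = 0.83 |
| 15% | 30% | 1.00 | 0.70/0.85 = 0.82 |
| 10% | 30% | 1.00 | 0.70/0.90 = 0.78 |
| 10% | 30% | 1.25 | 1.25 × 0.778 = 0.97 |
| 10% | 30% | 1.50 | 1.50 × 0.778 = 1.17 |

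The last two rows show masking: a true 25% excess of admissions all but disappears, and a 50% excess shrinks to 17%. The type with more early deaths appears protective only if R is below (1 − m1)/(1 − m2). That limit is 0.90/0.75 = 1.20 for 10% versus 25%, and 0.90/0.70 = 1.29 for 10% versus 30%.

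**Check by simulation.** The client follow-up window is stated: "Follow-up of clients happens from March 2011 until July 2013", about 28 months. A simulation over 28 months with equal admission rates gave ratios of 0.90 for 10% versus 20% (formula 0.80/0.90 = 0.89) and 0.79 for 10% versus 30% (formula 0.78). It gave 1.00 for equal shares.

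**What adjustment does.** The Cox model removes the part of the difference in early mortality that the Table 2 variables explain. With no diagnosis, comorbidity or prognosis variable among them, some may remain; the documents do not allow its size to be estimated. The incidence rates and cumulative incidence by type are described without adjustment and carry the distortion in full.

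**The case against.** The strongest defence is that the threshold is deliberate. Both sections use essentially the same limit, the event is meant to be permanent institutionalization, and respite care is among the standard services named in the Background. Temporary stays are foreseeable, and a duration rule is a reasonable way to exclude them. Before day 90 nobody can say for certain that a move was permanent. Counting every death in residential care as an event would bring in deaths during temporary stays, which could add events to the types with sicker clients. This stands. It is a good reason not to replace the current definition.

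A reader might go further than the documents allow in three ways:

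- **That the types with the sickest clients will look protective.** This does not follow. Early death after admission must differ between types, and sicker clients may also be admitted more often, which offsets or reverses the effect, as the last two rows of the second table show.
- **That the plan expects case mix to differ.** Research question 1 only asks whether it does. All projects were asked to recruit to the same age and frailty criteria. That sets a floor for frailty without guaranteeing equal prognosis.
- **That a hospital stay breaks the 90 days.** This is a literal reading of the word consecutive. The article states no rule on interruptions, and the full protocol may settle the matter. The early-death problem does not depend on it.

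It is also fair to say that the ratios above ignore the planned Cox adjustment, which covers much of the functional and cognitive case mix.

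**Conclusion.** The concern holds in a conditional form. It is certain that a client who moves into residential care and dies there before day 90 cannot be an event; this follows from the stated definition and exit rules. Whether it biases the comparison of types depends on whether early death after admission differs between them, and the documents do not say.

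Under assumed gaps of 0 to 20 percentage points and equal true admission rates, the unadjusted ratio runs from 1.00 down to 0.78. Adjusted estimates would be affected less, by an unknown amount. The definition is defensible as a way to exclude temporary stays, but on its own it is a weak basis for ranking non-randomized project types.

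**What to change.** Keep the current definition and prespecify a companion analysis beside it. In the companion analysis the event is an admission to residential care that is not followed by a return home within 90 days: the client either stays more than 90 days or dies while resident. Date it at admission. Report both for the crude rates, the cumulative incidence and the Cox model, and draw a conclusion on the ranking of types only where the two agree.

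Add one sentence saying that hospital days within a residential stay do not restart the 90-day count. The planned IMA linkage covers "medication use, hospital days, medical, nursing and physical therapy use", so such days can be identified.

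Two details need settling. Follow-up ends when a client leaves the project, so if admission itself ends participation, residence and death up to day 90 must come from the linked data. Admissions in the last 90 days before July 2013 also need a stated rule, because their full 90 days cannot be observed.

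The cost is a few lines of text and a second derivation of the event. No new data collection appears necessary, provided that the linkage shows residential stays for project clients. The article foresees using IMA to separate institutionalized from home-dwelling people in the control group, but does not say so for project clients. The downside is that some temporary stays ending in death will count as events in the companion analysis, which is why it should accompany the current definition and not replace it.

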## Background

Older people usually prefer staying at home rather than going into residential care [1-3]. Several organizations and professionals provide care for older people at home. In 1994, the World Health Organization defined home care as “an array of health and social support services provided to clients in their own residence. The assumption is that these co-ordinated services may prevent, delay or be a substitute for temporary or long-term institutional care” [4]. A more recent definition of home care defines it as “a phenomenon in which care is provided by professionals to people in their own homes with the ultimate goal of not only contributing to their life quality and functional health status, but also to replace hospital care with care in the home for societal reasons”. In this definition, home care covers a wide range of activities, from preventive visits to end-of-life care [5]. According to the 2009 WHO-report, an appropriate balance between care settings for elderly care is necessary, including supported self-care and home-based service. The report emphasizes the need for interventions to help maintain older people at home and to prevent long-term institutional care [6].

In the literature, several studies about predictors for home care use can be found. The most predominant ones are age, living arrangement, number of informal caregivers, income, medical diagnosis and functional status [1,7]. Moreover, randomized controlled trials have shown that targeted home care can contribute significantly to reduce hospital admission, to delay institutionalization and to improve quality of life [8-10].

In Belgium, 125.000 older people received home care services in 2010 and by 2025 this number will have increased up to 149.000, according to population prognoses [11]. The Belgian National Institute for Health and Disability Insurance (NIHDI)^a^ wishes to invest in home care by financing innovative projects that effectively help older people to stay at home longer. In this study, the effects of these innovative projects are examined as to whether they do keep frail older people longer at home, whether they maintain or improve their quality of life and whether they preserve their autonomy [12-15].

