### Research questions

The aim of the study is to answer the following research questions:

1. Do characteristics of populations differ between projects?

2. Which types of projects are associated with less decrease of the functional and cognitive performance of frail older persons?

3. Which types of projects contribute to a better quality of life of frail older persons?

4. Which types of projects are associated with a decreased risk of institutionalization of frail older persons?

5. Is the interRAI Maple scale a good predictor of institutionalization in our study?

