### Analyses

 – Research question 1 - Do characteristics of populations differ across projects?

In order to answer this first research question comparisons will be made between the populations in the different types of projects to explore whether they present particular characteristics. In these comparisons we will use the variables shown in Table 2 Frequencies will be calculated for categorical variables and means and medians with confidence intervals for continuous variables. Other possible comparison will be done by analysis of variance. All the statistical analysis in the study will be performed with the software Stata 11.1.

 – Research question 2 - Which types of projects are associated with less decline of the functional and cognitive performance of frail older persons?

 – Research question 3 - Which types of projects contribute to a better quality of life of frail older persons?

**Table 2 T2:** Variables to characterize the population of the study

**Topic**	**Variable**	**Source**	**Type of variable**
General information	Civil status	InterRAI HC	Qualitative
	Age	InterRAI HC and IMA	Continuous
	Gender	InterRAI HC and IMA	Dichotomic
Quality of Life	WHOQOL items score	WHOQOL-8	Continuous
Socio-economic status	Financial difficulties	InterRAI HC	Dichotomic
Primary caregiver’s burden	Zarit Burden score	ZBI-12	Continuous
Functional status	Katz score	IMA	Qualitative
	interRAI ADL hierarchy scale	InterRAI HC	Ordinal (0 to 6)
	interRAI IADL scales	InterRAI HC	Ordinal (0 to 48)
	interRAI Communication scale	InterRAI HC	Ordinal (0 to 8)
	interRAI CPS2 scale	InterRAI HC	Ordinal (0 to 6)
	interRAI DRS scale	InterRAI HC	Ordinal (0-14)

Longitudinal analyses will be performed to answer the second and third research questions. Outcome variables will be the interRAI ADL hierarchy scale, the interRAI CPS2 scale and the WHOQOL scale. Mean will be compared between arms of the study and covariate analysis (ANCOVA) will be done to control results for potentially confounding variables.

 The ADL hierarchy scale is a measure of a person’s functional performance. It is based on the concept of early, middle and late loss of ADLs and consists of 4 items from the interRAI instruments: personal hygiene, toilet use, locomotion and eating. The scores vary from 0 to 6 and the higher the score, the greater the dependency [36,37].

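### The Cox model for institutionalization does not hold the Table 2 covariates at their inclusion values, so on its natural reading it adjusts away part of the project effect

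*Protocol article*

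**What the plan says.** Under Analyses, research question 4, the event is fixed: "the definitive institutionalization (more than 90 consecutive days in residential care) will be used as event". The multivariate Cox model is given a causal purpose; it "will allow us to isolate the effects of the intervention from the effects of confounding variables". The adjustment set follows: "In this analysis we will use the variables of Table 2 as confounding variables". The paragraph closes with a further advantage claimed for the analysis, that "it takes into account the variability of covariates across time which makes it very appropriate for longitudinal studies".

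Table 2 lists, among others, the WHOQOL item scores, the Zarit burden score, the Katz score and the interRAI ADL hierarchy, IADL, Communication, CPS2 and DRS scales. For research questions 2 and 3 the same section states: "Outcome variables will be the interRAI ADL hierarchy scale, the interRAI CPS2 scale and the WHOQOL scale". Under Data collection, the interRAI HC, WHO-QOL-8 and ZBI-12 are completed at inclusion, at 6 months, every 6 months after that while the client stays in the project, and at exit.

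**The concern.** The plan gives the same scores two roles. In research questions 2 and 3 they are things that a project may change. In research question 4 they are confounders of the project effect. Both roles are compatible only if the second uses values from before the project could act. A score measured after inclusion that the project has altered lies on the path from project to institutionalization. Holding it constant leaves only the effect that does not pass through it.

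The study's main goal is to find which project types delay institutionalization most, so the comparison between types is what matters. Time-updated adjustment takes most from a type that works by preserving function and nothing from a type that works in another way. The order of the types can therefore change.

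**Working it through.** **Step 1: the text side by side.**
- Purpose: isolate the intervention effect (Analyses, research question 4).
- Adjustment set: all of Table 2, with no mention of baseline or inclusion values.
- Time: change in covariates is named as a strength of this analysis, in the same paragraph that names the set.
- Overlap: the ADL hierarchy, CPS2 and WHOQOL are in Table 2 and are also the outcomes of research questions 2 and 3.
- Hypothesised effect on those scores: "Which types of projects are associated with less decrease of the functional and cognitive performance of frail older persons" and "Which types of projects contribute to a better quality of life of frail older persons" (Research questions).
- Availability: post-inclusion values exist by design (Data collection).

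The article's own definition of a confounder requires an extraneous variable. A post-inclusion score that the project may alter does not meet it. The inclusion value does.

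**Step 2: size.** The article gives no figure on this point to reproduce, and none from which the loss could be computed. Two simulations show the range. All their parameters are assumptions. The share lost is 1 − ln(HR with time-updated score) / ln(HR with baseline score).

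*Illustration A.* 20,000 clients, project or no project at random (so there is no confounding), five 6-month intervals. The score starts as a standard normal variable and worsens by 0.25 per interval (noise SD 0.4). The project changes the drift by a, with a = 0, −0.1 or −0.2 per interval. The hazard per interval is 0.05 × exp(d·project + 0.5·current score), where d is the log of the direct hazard ratio.

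| Project effect | HR, baseline score | HR, time-updated score | Share of log HR lost |
|---|---|---|---|
| a = 0, direct HR 0.70 | 0.70 | 0.70 | none |
| a = −0.1, direct HR 0.80 | 0.75 | 0.83 | 1 − 0.186/0.288 = 35% |
| a = −0.2, direct HR 0.80 | 0.64 | 0.79 | 1 − 0.236/0.446 = 47% |
| a = −0.2, no direct effect | 0.85 | 1.04 | all |

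Unrounded hazard ratios (0.753 and 0.834; 0.642 and 0.786) give 36% and 46%. In the last row there were 5,657 events, so the standard error of the log HR is about 2/√5,657 = 0.027. The value 1.04 (log 0.039) is within simulation error of 1.

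A hand check agrees. With a = −0.2 the mean score shift over the five intervals is (0 + 0.2 + 0.4 + 0.6 + 0.8)/5 = 0.4. The indirect log HR is then about −0.5 × 0.4 = −0.2, or HR 0.82 against 0.85 simulated. Adding ln 0.80 = −0.223 gives HR 0.66 against 0.64 simulated.

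*Illustration B.* 12 runs of 3,000 clients over 28 months (the length of March 2011 to July 2013), with ADL updated every 6 months and the hazard multiplied by 1.65 per ADL point. The project halves ADL decline from 0.10 to 0.05 points per month and has no other effect. The mean log HR is −0.361 (HR 0.70) with baseline ADL and −0.062 (HR 0.94) with time-updated ADL. The loss is 1 − 0.062/0.361 = 83%.

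**Step 3: ranking.** Take from Illustration A a type with a = −0.2 and direct HR 0.80, and a type with direct HR 0.70 only. With baseline adjustment they rank 0.64 before 0.70. With time-updated adjustment they rank 0.79 behind 0.70. The order reverses.

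**The case against.** The strongest reply is that the article never specifies a time-updated model. It states two things separately: Table 2 supplies the confounders, and the method can handle covariates that change, which may be a general remark about Cox regression. Table 2 is titled as a description of the study population, and confounders are defined as extraneous. Both favour baseline values. A condensed article may also leave covariate timing to a fuller document. This stands so far: time-updating is the natural reading, not an explicit specification. It does not dispose of the point, because the remark is made about this analysis, in the paragraph that names the covariates, and nothing limits them to inclusion.

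Second, adjusting for ADL, CPS2 and WHOQOL is not wrong in itself. In a non-randomized comparison their inclusion values are needed. That is right; the problem lies only in values measured later.

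Third, the incidence rates and cumulative incidence by project type are untouched by time-updated covariates. That is also true, but nothing in the article says they are adjusted for differences between client populations, so they do not replace the Cox comparison.

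A reader might also infer that the covariate set leaves out required predictors, since the Background says "The most predominant ones are age, living arrangement, number of informal caregivers, income, medical diagnosis and functional status" and Table 2 has no living arrangement, number of informal caregivers or medical diagnosis. The article does not support this. That list concerns predictors of home care use, not institutionalization. IMA data, including hospital days, are already to be added to the analysis for project clients. The article does not establish that the number of informal caregivers or a dementia diagnosis is recorded for every client.

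**Conclusion.** The point holds on the natural reading of the research question 4 paragraph: post-inclusion values of scores that the projects are meant to influence would enter the Cox model as confounders, and the model would no longer estimate the total project effect it is meant to isolate. This touches the study's main comparison and should be settled before the analysis.

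The loss depends on two links: projects change the scores, and the scores predict institutionalization. The study asks about the first, and its choice of confounders presumes the second. Under assumed parameters the loss is none without the first link, about 35% to 47% of the log hazard ratio with mixed effects, and nearly all of it under full mediation.

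A reader might take 83% as the expected loss, or conclude that effective projects will show hazard ratios near 1. The documents do not support that: both results come from scenarios in which the project acts only through function. Reversal of the ranking is possible, not shown to be likely. If the scores and institutionalization share unmeasured causes, the bias could also run in another direction.

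**What to change.** State in the research question 4 paragraph that the primary Cox model for the project effect uses the value at inclusion of every Table 2 variable. State also that models with time-updated covariates are secondary prognostic or mediation analyses and are not reported as the effect of a project type. Reword or remove the sentence that presents covariate variation over time as an advantage, so that it does not describe the primary model.

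The cost is a sentence or two. The interRAI, WHO-QOL-8 and ZBI-12 scores are already collected at inclusion, so they need no new data. The Katz score comes from IMA, so the text should say which record counts as the inclusion value. The downside is that the primary model does not use later covariate values; these remain available for the secondary analyses.
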